### Follow-up

After the procedure, all included patients will receive follow-up in outpatient clinics at 1, 6, and 12 months and annually thereafter. The required routine examinations include history taking, physical examination, blood biochemical index and duplex ultrasound. All biological specimens will be processed in routine procedure and not be used in ancillary or other studies. The computed tomography angiography will be performed to search for detailed information if any adverse event, especially endoleak or limb thrombosis, is found by duplex ultrasound. Patients who are unable to return to the outpatient clinic will be suggested to undergo duplex ultrasonography or computed tomography in local medical institutions, which will send medical records and images back to researchers. For patients who fail to finish the expected follow-up, telephone interview or WeChat message will be used instead to record survival status and postoperative adverse events. Due to no additional harm induced by the trial, all adverse events will be processed according to normal treatment procedure and patients will not automatically quit the group or receive additional compensation.

Patients are defined as dropout if the following events occur: (1) Fail to complete the expected follow-up and could not obtain image or medical records: a subject is considered lost to follow-up if they could not be contacted *via* five attempts by telephone or WeChat message. (2) Make withdrawal consent: all participants have the right to withdraw from the study at any time for any reason without obstruction.

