### Outcomes of interest

The primary outcome is 3-year freedom from MALEs, which involves type IB/III endoleak and limb occlusion. Type IB endoleak is defined as persistent direct flow in the aneurysm sac due to inadequate distal seal of the stent graft. Type III endoleak is defined as persistent direct flow resulting from stent graft component separation or fabric tear. Limb occlusion is defined as a total occlusion occurring in limb grafts, regardless of symptoms, or an invasively treated stenosis resulting from thrombus formation (> 50% lumen reduction).

The secondary outcomes involve 3-year freedom from type IA endoleak and 3-year freedom from aortic reintervention. Type IA endoleak is defined as persistent direct flow in the aneurysm sac due to inadequate proximal seal of the stent graft. Aortic reintervention refers to any secondary surgical procedure related to the index EVAR.

Other outcomes consist of three aspects: intraoperative technical outcomes (operation time, radiation exposure time, dosage of contrast medium and technical success rate); short-term postoperative outcomes (length of stay in intensive care unit or vascular ward, acute kidney injury, 30-day overall morbidity, 30-day major adverse cardiac events, 30-day all-cause mortality); long-term outcomes (renal function decline, occurrence of type I/II/III endoleak or stent migration, freedom from major adverse cardiac events, aneurysm related death, overall survival).

Detailed information for outcomes is listed in Table 2.

**TABLE 2 T2:** Detailed information for outcomes.

Outcomes	Definition

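### Telephone or WeChat contact can stand in for imaging of a largely imaging-defined primary outcome, and the dropout rule disagrees with itself about patients who are reachable but unimaged

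*Protocol article*

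**What the plan says.** All references are to the protocol article.

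- **Imaging at visits (Follow-up).** Visits are at 1, 6 and 12 months and then yearly. "The required routine examinations include history taking, physical examination, blood biochemical index and duplex ultrasound". CT angiography follows when duplex shows an adverse event; the text names endoleak and limb thrombosis as the leading examples.
- **Patients who cannot attend (Follow-up).** They "will be suggested to undergo duplex ultrasonography or computed tomography in local medical institutions", with images and records sent back. This is a suggestion, not a requirement.
- **Patients who do not finish follow-up (Follow-up).** For them, "telephone interview or WeChat message will be used instead to record survival status and postoperative adverse events".
- **Dropout item (1) (Follow-up).** Its first half reads "Fail to complete the expected follow-up and could not obtain image or medical records". After a colon it continues: "a subject is considered lost to follow-up if they could not be contacted" in five attempts by telephone or WeChat.
- **Primary outcome (Outcomes of interest).** "The primary outcome is 3-year freedom from MALEs, which involves type IB/III endoleak and limb occlusion". Occlusion is "a total occlusion occurring in limb grafts, regardless of symptoms", or an invasively treated thrombotic stenosis above 50%.
- **Design (Sample size calculation).** Non-inferiority on the risk difference, margin 0.15; planning event rates 11.5% (crossed limb, CL) and 7.9% (standard limb, SL); 20% dropout; 73 CL and 202 SL patients.

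**The concern.** An endoleak without symptoms and a silent limb occlusion are seen only on imaging, and the outcome definition counts both. Yet the plan names telephone or messaging as the replacement source of adverse-event data when follow-up is incomplete, and the same section treats endoleak and limb thrombosis as adverse events. Nothing in the article limits what may be concluded from a call in which the patient reports no problem.

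The dropout rule should catch these patients, but it gives two answers for them. That also leaves unclear whom the 20% dropout allowance covers.

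The stake is specific to a non-inferiority comparison. Events that go unseen at a similar rate in both groups make a truly worse group look closer to the other, so poor ascertainment can help the trial reach its claim. Surgeons and patients are unblinded (Allocations of intervention), so equal ascertainment in the two groups cannot be taken for granted either.

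**Working it through.** **1. The dropout rule applied to one patient.** Take a patient who answers the telephone at 36 months, has had no recent duplex or CT, and for whom no records can be obtained.

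- First half of item (1): follow-up incomplete, no image or records, so a dropout.
- Second half: reached within five attempts, so not lost to follow-up.

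The two halves disagree about exactly the patients whose primary outcome is unknown.

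**2. The plan's own sample size.** Non-inferiority of two proportions, unpooled variance, one-sided 5% (the article does not state the sidedness), 80% power:

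n(SL) = (1.645 + 0.842)² × [0.115 × 0.885 / (4/11) + 0.079 × 0.921] / (0.15 − 0.036)² = 6.183 × 0.3526 / 0.0130 = 167.8, so 168; n(CL) = 168 × 4/11 = 61.1.

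Multiplying by 1.2 gives 201.6 and 73.3, that is 202 and 73. The stated figures reproduce, so one-sided 5% is used below.

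**3. Effect of missed events.** Let f be the share of patients followed by telephone only and s the share of their MALEs that go unnoticed. The documents give neither; both are assumptions. If such patients were analysed as event-free, then

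recorded rate = true rate × (1 − f × s).

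With f × s equal in both groups, the risk difference shrinks by the same factor. The false non-inferiority rate is evaluated at the margin, with true rates 22.9% and 7.9% and 73/202 analysed. The exact column sums binomial probabilities over all outcomes whose one-sided 5% Wald upper limit lies below 0.15.

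| Events missed, both groups (f × s) | Recorded rates CL / SL | Recorded difference | False non-inferiority, exact | Normal approximation |
|---|---|---|---|---|
| 0 | 22.9% / 7.9% | 15.0 points | 6.8% | 5.0% |
| 10% | 20.6% / 7.1% | 13.5 points | 11.5% | 8.9% |
| 16% (f = 20%, s = 80%) | 19.2% / 6.6% | 12.6 points | 15.5% | 12.3% |
| 20% | 18.3% / 6.3% | 12.0 points | 18.8% | 15.3% |

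About 2 points of the starting 6.8% come from the Wald limit itself and have nothing to do with follow-up. With 58/162 analysed (20% lost), missing 20% of events gives 17.3% by the exact calculation.

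**4. Direction.** Let k be the missed fraction in each group. The recorded difference falls below the true one only if

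k(SL) × p(SL) < k(CL) × p(CL), that is k(SL)/k(CL) < p(CL)/p(SL).

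The bound is 0.115/0.079 = 1.46 at the planning rates and 0.229/0.079 = 2.90 at the margin. Beyond it the bias runs the other way. With 20% missed in SL and none in CL, the planning difference rises from 3.6 to 11.5 − 7.9 × 0.8 = 5.2 points, and the probability of concluding non-inferiority falls from 86% to 77% (normal approximation). With equal true rates and equal missing, the difference stays at zero.

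**The case against.** The strongest reply is that the article nowhere says a telephone-only patient is scored MALE-free. A reader might infer that imaging-only events are recorded as absent, but the text says only what the contact is used to record. The Statistical analysis section names Cox regression and a marginal structural model, which allow censoring at the last imaging, and a full protocol or SAP may contain that rule. This stands: scoring as event-free is a possible consequence of the wording, not a stated rule.

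A reader might also infer that telephone contact takes the patient out of the dropout definition. The documents do not support that, because the first half of item (1) covers a patient with no image or records. What can be shown is the contradiction between the halves.

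Third, a reader might infer that the comparison is necessarily biased toward non-inferiority. Step 4 shows that it is not. A proportional loss of events also leaves a ratio measure largely unchanged; the attenuation concerns the risk difference, which is the scale of the margin.

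Finally, the missed share may be modest. Patients may have been scanned at several visits before missing one, local imaging is offered, and treated or symptomatic events can be reported by telephone. These points limit the size. They do not remove the gap, because the wording still lets conversation replace imaging for events that conversation cannot exclude, and the dropout rule still gives two answers.

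**Conclusion.** The concern holds in a limited form. Followed as written, the Follow-up section can under-ascertain the primary outcome, and dropout item (1) contradicts itself about reachable but unimaged patients. Both rest on the article's own wording and do not depend on what an SAP might add.

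The size is a conditional illustration. If CL is truly 15 points worse, under-detection is similar in both groups and unimaged patients are analysed as event-free, missing 10% to 20% of events raises false non-inferiority from about 7% to between 11.5% and 19%. At the planning rates, 20% missed in both groups moves the difference only from 3.6 to 2.9 points. The missed fractions are assumptions, and the direction depends on how missing is distributed between the groups.

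**What to change.** - Make the two halves of dropout item (1) agree on patients who can be contacted but have no images or records.
- State that MALE-free status, and freedom from each endoleak or occlusion outcome, requires duplex or CT that assessed the graft. Censor these outcomes at the last adequate imaging.
- Use telephone and WeChat information only for survival, reintervention and externally documented events.
- Count patients without outcome imaging as missing within the 20% allowance.
- Add a sensitivity analysis that gives unimaged patients different event rates by group, including a higher rate in CL.

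The cost is a few sentences, a field for the date of last graft imaging, and somewhat fewer evaluable patient-years. If unimaged patients are counted as not evaluable, power at the planning rates (normal approximation, one-sided 5%) is about 78% at 20% total loss (58/162), 74% at 30% (51/141) and 68% at 40% (44/121). The change is best made while follow-up is running, since imaging not obtained cannot be recovered later.

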### Outcomes of interest

The primary outcome is 3-year freedom from MALEs, which involves type IB/III endoleak and limb occlusion. Type IB endoleak is defined as persistent direct flow in the aneurysm sac due to inadequate distal seal of the stent graft. Type III endoleak is defined as persistent direct flow resulting from stent graft component separation or fabric tear. Limb occlusion is defined as a total occlusion occurring in limb grafts, regardless of symptoms, or an invasively treated stenosis resulting from thrombus formation (> 50% lumen reduction).

The secondary outcomes involve 3-year freedom from type IA endoleak and 3-year freedom from aortic reintervention. Type IA endoleak is defined as persistent direct flow in the aneurysm sac due to inadequate proximal seal of the stent graft. Aortic reintervention refers to any secondary surgical procedure related to the index EVAR.

Other outcomes consist of three aspects: intraoperative technical outcomes (operation time, radiation exposure time, dosage of contrast medium and technical success rate); short-term postoperative outcomes (length of stay in intensive care unit or vascular ward, acute kidney injury, 30-day overall morbidity, 30-day major adverse cardiac events, 30-day all-cause mortality); long-term outcomes (renal function decline, occurrence of type I/II/III endoleak or stent migration, freedom from major adverse cardiac events, aneurysm related death, overall survival).

Detailed information for outcomes is listed in Table 2.

**TABLE 2 T2:** Detailed information for outcomes.

Outcomes	Definition

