**Methods:**

This is a prospective, single-center, non-randomized controlled trial. A total of 275 patients who meet the inclusion criteria will be enrolled and allocated with a 4:11 ratio of CL to SL, which is based on results of our previous study. All patients will receive same perioperative management and postoperative medications. All EVAR procedures will be performed under standard protocol, utilizing Endurant II or IIs Stent Graft. The configuration of the graft stent will be decided by surgeons and confirmed by final angiography. The primary outcome is 3-year freedom from major adverse limb-graft events (MALEs). Endpoints will be assessed at the following time points: 1, 6, 12, 24, and 36 months.

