### Allocations of intervention

Based on the anatomic features of the aneurysm by intraoperative imaging, surgeons will determine whether to adopt CL or SL configuration. When both configurations are feasible, surgeons will assign the limb configuration based on covariate adaptive matching between the two groups. The major matched covariates are as follows: age, gender and aneurysm diameter. Both surgeons and participants are not blinded to the interventions, and only statisticians who analyze the data are blinded.

The CL and SL configurations are defined as crossed or uncrossed limb grafts in anteroposterior view of the final angiogram, respectively. CL is further subdivided into anterior-posterior (AP) cross and left-right (LR) cross, which correspond to ≥ 50 and < 50% overlapped areas between two limb grafts in the angiogram. SL is similarly subdivided into AP parallel and LR parallel with the same definition.

The included patients will receive the same perioperative management, including blood pressure control, analgesia and medication with antiplatelets and statins. In interventional operating room, both common femoral arteries will be used for percutaneous or cut down access. After administration of 0.5 mg/kg unfractionated heparin, graft stents are placed in accordance with instruction for use by an experienced surgeon of vascular surgery. Treatment procedures are performed under a standard protocol. The Endurant II or IIs Stent Graft (Medtronic, Minneapolis, Minn) is used for repair.

Postoperative medications include antiplatelet monotherapy (aspirin 100 mg once a day or clopidogrel 75 mg once a day) and statins. Patients are expected to take these medications all life unless severe adverse event occurs. Anticoagulants, such as low molecular weight heparin or direct oral anticoagulants, will be used according to surgeons’ decision.

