**Primary outcome**	
3-year freedom from MALEs	Free of type IB, III endoleak and limb occlusion within 3 years

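### A thrombotic limb stenosis above 50% enters the primary endpoint only if it is treated invasively, so an unblinded treatment decision is part of the event definition

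*Protocol article*

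**What the plan says.** Protocol article, Outcomes of interest: "The primary outcome is 3-year freedom from MALEs, which involves type IB/III endoleak and limb occlusion". Limb occlusion then has two routes. The first carries no treatment condition: "Limb occlusion is defined as a total occlusion occurring in limb grafts, regardless of symptoms". The second is conditional on treatment: "or an invasively treated stenosis resulting from thrombus formation (> 50% lumen reduction". The primary-outcome row of Table 2 adds no third route: "Free of type IB, III endoleak and limb occlusion within 3 years".

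Allocations of intervention states that "Both surgeons and participants are not blinded to the interventions, and only statisticians who analyze the data are blinded". It also has surgeons choose the configuration from intraoperative imaging, with covariate matching only where both configurations are feasible.

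Follow-up requires duplex ultrasound at each clinic visit. CT angiography follows if duplex shows an adverse event, limb thrombosis being one of the examples named. Adverse events are handled under usual care. Patients who do not complete the visits are followed by telephone or WeChat message.

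Sample size calculation assumes adverse limb events in 11.5% of CL and 7.9% of SL patients, a non-inferiority margin of 0.15 on the risk difference, error rates of 0.05 and 0.2, a 4:11 ratio and 20% dropout. This gives 73 CL and 202 SL patients.

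**The concern.** Two patients with the same 60% thrombotic stenosis on duplex can be scored differently. The one who has an invasive procedure has a primary event. The one who is managed in any other way remains event-free, unless the limb later occludes completely or a type IB or III endoleak appears. The difference lies in what was decided, and those deciding know the configuration.

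Blinding the statistician does not help, because the event is created or not created in the clinic. The propensity score uses demographic and anatomic information, so weighting can balance who received each configuration but cannot recover a later lesion that was never scored. The reintervention outcome also depends on treatment and would miss the same lesion. No other listed follow-up outcome names an untreated stenosis.

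At stake is whether the non-inferiority result reflects limb patency or a difference in readiness to intervene.

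**Working it through.** **1. How the definition scores each case**

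- Total occlusion, with or without symptoms: event.
- Thrombotic stenosis above 50%, treated invasively: event.
- Thrombotic stenosis above 50%, not treated invasively: no event, unless it progresses to total occlusion or another component occurs.

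**2. The plan's own sample size, to obtain the evaluable numbers**

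Inputs are those of Sample size calculation. One-sided 0.05 is an inference, because the article does not state sidedness.

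- Variance term per SL patient: 0.115 × 0.885 / (4/11) + 0.079 × 0.921 = 0.2799 + 0.0728 = 0.3526.
- Distance to the margin: 0.15 − (0.115 − 0.079) = 0.114.
- SL patients: (1.645 + 0.842)² × 0.3526 / 0.114² = 168. CL patients: 168 × 4/11 = 61.1.
- Multiplied by 1.2: 201.6 SL and 73.3 CL, which matches 202 and 73.

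The evaluable numbers are therefore 61 CL and 168 SL as planned. A strict 20% loss from 73 and 202 leaves 58 and 161 (58.4 and 161.6, rounded down). Expected events at the planning rates, all components together, are 0.115 × 61 = 7.0 in CL and 0.079 × 168 = 13.3 in SL.

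**3. Weight of one lesion**

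- One net unscored CL lesion: 1/61 = 1.6 points to 1/58 = 1.7 points, about 11% of the 15-point margin. It lowers the apparent CL excess.
- One net unscored SL lesion: 1/168 to 1/161, both 0.6 points. It raises the apparent CL excess.

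**4. When there is no shift**

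If a share u of patients in each group has an unscored stenosis, the observed difference is (p_CL − u) − (p_SL − u) = p_CL − p_SL. Equal under-counting cancels on the risk-difference scale, where the margin is set.

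**5. Illustration in both directions (assumed shares, not taken from the documents)**

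All use 58 CL and 161 SL, SL risk 7.9% and one-sided 0.05.

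- *Toward non-inferiority.* Suppose the true difference, counting all stenoses above 50%, is exactly 0.15 (CL risk 22.9%), and a share x of CL patients goes unscored, with none in SL. The chance of declaring non-inferiority is Φ(x/SE − 1.645). For x = 0.02, SE = √(0.209 × 0.791/58 + 0.079 × 0.921/161) = 0.0575, so Φ(0.348 − 1.645) = 0.097. The false-positive rate goes from 5% to about 7% for x = 0.01 and about 10% for x = 0.02. The second value is roughly one CL patient (0.02 × 58 = 1.2).
- *Against non-inferiority.* Suppose even-handed scoring would give 11.5% and 7.9%, but readier intervention in CL limbs scores a further share of CL patients. Power is 78% with no extra share, 69% with 0.01 and 60% with 0.02. For 0.02, SE = 0.0497 and Φ((0.15 − 0.056)/0.0497 − 1.645) = 0.60.

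**The case against.** The definition is explicit and nothing else in the article contradicts it. Requiring treatment as well as narrowing above 50% keeps incidental duplex readings out, and the anatomic threshold keeps trivial interventions out. An untreated stenosis that goes on to occlude completely within three years still counts. Preferring a lesion-only definition is partly a matter of taste. Such a definition also has a cost: a procedure can be reported by telephone, while an untreated, symptomless stenosis cannot. It also moves unblinded judgement from treatment to the grading of images. All of this stands. It argues against replacing the primary definition outright, but not against a parallel analysis.

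Three stronger readings are tempting, and the documents do not support them.

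- A reader might infer that CL stenoses will be managed with anticoagulants and so escape scoring, since "Anticoagulants, such as low molecular weight heparin or direct oral anticoagulants, will be used according to surgeons’ decision". That sentence concerns postoperative medication in general. Nothing says a limb stenosis will be managed that way.
- A reader might see a contradiction with the abstract, where "All patients will receive same perioperative management and postoperative medications". The main text makes antiplatelet monotherapy and statins common to everyone and leaves anticoagulants to discretion. This is loose abstract wording and does not bear on the endpoint definition.
- A reader might conclude that the definition favours CL. The direction is unknown: surgeons wary of crossed limbs might intervene sooner, which would count against CL.

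**Conclusion.** The point holds in a limited form. One route into one component of the primary endpoint depends on a treatment decision made by surgeons who know the configuration, with no stated criterion for that decision. If the threshold for intervention differs between CL and SL, the risk difference is biased in either direction, and baseline weighting cannot correct it. With the same threshold and equally frequent uncounted lesions, there is no shift.

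The actual size cannot be derived, because the documents give no frequency of non-invasively managed stenosis. They also do not show whether the planning rates of 11.5% and 7.9% included untreated stenoses. The only firm figure is the leverage: with about 7 CL events expected, one net CL lesion is worth 1.6 to 1.7 points of a 15-point margin. The error and power figures in the working are illustrations under assumed shares.

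**What to change.** Keep the current definition and prespecify a second analysis of the primary endpoint, reported beside it. In that analysis, limb occlusion is total occlusion or thrombus-related lumen reduction above 50% on duplex or CT angiography, whatever the treatment, dated at first imaging detection. State in advance that the non-inferiority conclusion will be interpreted in light of both versions. If they agree, the treatment condition did not drive the result. If they differ, the difference must be explained before non-inferiority is claimed.

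The cost is one definition sentence and a recorded lumen-reduction grade. The imaging is already in the follow-up schedule, and patient care does not change. Recording the grade without knowledge of later management would limit the judgement it introduces.

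There are two downsides. The event rate in the second analysis will be somewhat higher than planned if the earlier cohort counted treated stenoses only. Untreated stenoses will also be missed in patients followed only by telephone or WeChat, so the number of patients without imaging should be reported by group.
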